## Abstract

**Background:**

Breast cancer survivors (BCSs) are at a higher risk of developing insomnia. The negative effects of cancer-related insomnia (CRI) include depression, anxiety, fatigue, aggressive pain, impaired immune functioning, decreased quality of life, and even increased cancer mortality. Although preliminary progress has been made in the treatment of CRI with acupuncture, the evidence is insufficient and the neurological mechanism underlying the effect of acupuncture is still unclear.

**Methods:**

The study employs a single-blinded, randomized, controlled trial design. A total of 80 participants will be randomly allocated in a 1:1 ratio to either the treatment group (*n* = 40) or the control group (*n* = 40). The former will receive acupuncture treatment, while the latter will receive sham acupuncture treatment. Both groups will receive 12 sessions over a 4-week period, three times per week (every other day), and each session will last for 30 min. Follow-up assessments will be conducted in week 8. The primary outcome will be the treatment response rate. Secondary outcomes include the change in Insomnia Severity Index (ISI), the treatment remission rate, actigraphy sleep assessment, Generalized Anxiety Disorder Scale (GAD-7), Patient Health Questionnaire-9 (PHQ-9), Quality of Life Core Scale (QLQ-C30), the weekly usage of remedial drugs, and functional magnetic resonance imaging (fMRI) analysis. Data for the outcomes will be collected at week 0 (the baseline), week 1 (the intervention period), week 4 (the post-treatment period), and week 8 (the follow-up period).

**Discussion:**

The objective of this study is to assess the efficacy of acupuncture for patients with CRI in comparison with sham acupuncture. Additionally, the research aims to explore the neuropathological mechanisms of CRI and provide the first evidence on the characteristics of acupuncture treatment using fMRI. We expect that the results of this study will provide valuable scientific evidence of acupuncture treatment for CRI.

**Clinical trial registration**: Chinese Clinical Trial Registry, identifier ChiCTR2300070349: https://www.chictr.org.cn/showproj.html?proj=188677.

## Background and objective

In recent times, breast cancer has overtaken lung cancer as the foremost cause of cancer incidence worldwide. According to the 2020 Global Cancer Observatory (GLOBOCAN) database, which covers 36 types of cancers in 185 countries, an estimated 2.3 million new cases of breast cancer have been reported. These cases account for approximately 11.7% of all cancer cases (1). While the survival rate for breast cancer survivors (BCSs) remains relatively high in most countries, it is imperative to address the significant issue of reduced life quality among them, especially cancer-related insomnia (CRI). Therefore, this particular concern has gained prominence as an important clinical priority.

A large proportion of BCSs, ranging from 53.5 to 79.6%, have experienced clinically elevated and persistent insomnia symptoms, both during and after completing treatment (2, 3). These symptoms encompass dissatisfaction with sleep quality or quantity and are characterized by difficulties of falling sleep, maintaining sleep, or experiencing early morning awakenings, which cause notable distress or impairment in daytime functioning (4). The situation may arise from psychological distress following a cancer diagnosis, concurrent cancer symptoms, and treatment-related side effects (5). Moreover, CRI further heightens the risk of psychological and physical morbidity, ultimately impacting the overall quality of life negatively (6, 7).

Presently, interventions for treating CRI encompass both pharmaceutical and non-pharmaceutical approaches. However, commonly employed sedative and hypnotic drugs, despite their rapid onset of action, often come with various sequelae, withdrawal effects, dependence, and addiction (8). Hence, there is significant value in exploring complementary and alternative therapies that offer effective outcomes with minimal side effects. A growing interest in acupuncture therapy has revealed its potential to enhance sleep quality while addressing mental and emotional distress symptoms (9). Nevertheless, the limited study designs of previous research diminish the persuasiveness of the evidence, and the underlying mechanism of acupuncture remains incompletely understood (10, 11).

Therefore, the purpose of this study is to examine the clinical efficacy and safety of acupuncture in treating CRI. Our investigation will comprehensively assess patients’ sleep through subjective and objective measures. Furthermore, due to the lack of functional imaging studies on CRI, this trial will incorporate functional magnetic resonance imaging (fMRI) to explore the potential neural mechanisms underlying the effectiveness of acupuncture in treating CRI.

## Methods

### Study design

As a randomized, single blinded, sham-controlled trial, this study has been registered in the Chinese Clinical Trial Registry (ChiCTR2300070349). The protocol is based on the Standard Protocol Items: Recommendations for Intervention Trials (SPIRIT) 2013 in Supplementary File 1. This study was approved by the Medical Ethics Committee of LongHua Hospital Shanghai University of Traditional Chinese Medicine (SHUTCM) (NO.2023-LHXS-009). Any modifications to the protocol will be reported to both the ChiCTR and the Medical Ethics Committee. The flowchart of the study is shown in Figure 1, while the schedule of enrollment, interventions, and assessment is shown in Table 1.

**Figure 1 fig1:**
[figure not shown]
Flowchart of the study. ISI, Insomnia Severity Index; GAD-7, Generalized Anxiety Disorder Scale; PHQ-9, Patient Health Questionnaire-9; QLQ-C30, Quality of Life Core Scale; fMRI, Functional Magnetic Resonance Imaging.

**Table 1 tab1:** Schedule of enrolment, interventions, and assessments.

Study period	Enrolment		Intervention period				Follow-up period
Time point	Week-1	Week 0	Week 1	Week 2	Week 3	Week 4	Week 8
Eligibility screening	**×**						
Sign informed consent	**×**						
Medical history	**×**						
Randomization		**×**					
*Intervention*							
Acupuncture			**×**	**×**	**×**	**×**	
Sham acupuncture			**×**	**×**	**×**	**×**	
*Primary outcomes*							
Treatment response rate						**×**	
*Secondary outcomes*							
Treatment remission rate						**×**	**×**
Treatment response rate							**×**
Changes of ISI scores from baseline		**×**				**×**	**×**
Actigraphy sleep assessment		**×**	**×**			**×**	
GAD-7		**×**				**×**	
PHQ-9		**×**				**×**	
QLQ-C30		**×**				**×**	
fMRI		**×**				**×**	
Adverse events			**×**	**×**	**×**	**×**	
Weekly usage of remedial drugs			**×**	**×**	**×**	**×**	**×**
*Success of blinding*						**×**	

ISI, Insomnia Severity Index; GAD-7, Generalized Anxiety Disorder Scale; PHQ-9, Patient Health Questionnaire-9; QLQ-C30, Quality of Life Core Scale; fMRI, Functional Magnetic Resonance Imaging.

### Patient recruitment

A total of 80 patients with breast cancer-related insomnia will be recruited from both hospital websites and outpatient clinics at LongHua Hospital SHUTCM. Patients will undergo eligibility assessment based on predefined inclusion and exclusion criteria. Those who meet the criteria will provide informed consent and be randomly allocated in a 1:1 ratio to either the treatment group or the control group. In addition, 10 healthy subjects will also be recruited for this trial. Participants will have the right to withdraw from the trial at any time, and their personal data will be used exclusively for medical research purposes.

### Criteria for inclusion

For CRI patients, the inclusion criteria are as follows:

Meet the diagnosis of stage I to III breast cancer and also meet the DSM-IV diagnostic criteria for insomnia, the symptoms of which occurred after breast cancer diagnosis and lasted for at least 1 month.Aged 18 to 75 years, female.Eastern cooperative oncology group performance status score ≤ 2.Sleep severity index (ISI) score ≥ 8.Survival prediction ≥6 months.No prior acupuncture treatment.Right-handed.No MRI contraindications such as MR-incompatible metal implants or claustrophobia.Consent to participate and provide written informed consent.

For healthy subjects, the inclusion criteria are as follows:

Age-, hand dominance-, and educational level matched to the selected CRI patients.Self-reported good sleep quality with an ISI score of <8.Absence of previous functional or organic disease or history of head trauma.No MRI contraindications for the CRI patients.Consent to participate and provide written informed consent.

### Criteria for exclusion

For CRI patients, the exclusion criteria are as follows:

Insomnia associated with cancer pain (Numeric Rating Scale for Pain ≥4) or other physical and mental illnesses.Irregular sleep habits or night shift work.History of drug abuse or addiction.Patients who have taken sedative or hypnotic drugs over the past 2 weeks, accepted other treatment for insomnia over the past 3 months, or participated in other clinical trials over the last month.Scheduled for radiotherapy, chemotherapy, or surgery during the trial.Concomitant serious heart, liver, kidney, and other major diseases.Pregnant or breastfeeding.Inability to understand and complete the assessment scale.Ulcers, abscesses, and infections at the needling site.

For healthy subjects, the exclusion criteria are as follows:

Pregnant or breastfeeding.Irregular sleep habits or night shift work.

### Randomization, allocation concealment, and blinding

Randomization will be performed using random numbers generated by a professional statistician with SAS version 9.4 (SAS Institute Inc., Cary, NC, United States). An assistant will open an opaque envelope containing a random distribution card in the order matching the hospital visits to assign patients randomly to the treatment or control group. To ensure blinding, researchers will receive training and adhere to departmental separation principles. While blinding the acupuncturist is not possible, patients, outcome assessors, MRI scanner operators, and data analysts will be blinded. Patients will be scheduled at different times and placed in separate rooms to prevent interaction. A black patch will be worn during treatment to conceal acupoint locations and manipulation. Additionally, an acupuncture device will facilitate successful blinding. A blinding assessment will be conducted after treatment with the question: “Which intervention do you think you received, acupuncture treatment, sham acupuncture treatment, or uncertain?”

## Interventions

### Treatment group

Patients will be treated with a supine position at unilateral Shen Ting (GV 24), Yin Tang (GV 29), Zhong Wan (CV 12) and bilateral Nei Guan (PC 6), Shen Men (HT 7), San Yin Jiao (SP 6), Zhao Hai (KI 6), and Shen Mai (BL 62). Locations are determined according to the National Standard of People’s Republic of China (GB/T12346-2010) is shown in Figure 2, and the specific manipulating techniques are described in Table 2. In this group, sterile acupuncture needles from Suzhou Medical Supplies Factory Co.’s Huatuo (size 0.25*25 mm and 0.25*40 mm) will be used. Prior to needle insertion, routine disinfection will be performed, and acupuncture devices will be applied to each location. The acupuncture device is a hollow patch covered with an opaque medical tape on the top, adhering to the skin at the base (shown in Figure 3). For the acupuncture group, needles will be pierced through the patch into the skin and then manipulated by insertion, lifting and twisting to activate the patients’ sensation of “de qi,” characterized by sensations of swelling, soreness, numbness, and heaviness. Participants will receive three treatment sessions per week (every other day), each lasting for 30 min, for a total of 12 sessions over a 4-week period. Follow-up assessments will be conducted in week 8.

**Figure 2 fig2:**
[figure not shown]
Image of acupoints and control acupoints.

**Table 2 tab2:** Locations and manipulations of acupoints in the intervention group.

Acupoint	Location	Manipulation
Nei Guan (PC 6)	On the anterior aspect of the forearm, between the palmaris longus and flexor carpi radialis tendons and 2 *cun* proximal to the palmar wrist crease	Insert the needle perpendicularly for 0.5–1.0 *cun*
Shen Men (HT 7)	On the anterior and medial aspect of the wrist, radial to the flexor carpi ulnaris tendon at the palmar wrist crease	Insert the needle perpendicularly for 0.3–0.5 *cun*
Shen Ting (GV 24)	On the anterior midline of the head. This acupoint is found 0.5 *cun* superior to the anterior hairline	Insert the needle transversely for 0.5–0.8 *cun*
Yin Tang (GV 29)	At the midpoint between the medical ends of the eyebrows	Insert the needle transversely for 0.3–0.5 *cun*
Zhong Wan (CV 12)	On the anterior midline of the upper abdomen, 4 *cun* above the umbilicus	Insert the needle perpendicularly for 0.8–1.2 *cun*
Zhao Hai (KI 6)	On the medial aspect of the foot, in the depression inferior to the medial malleolus and 1 *cun* inferior to the prominence of the medial malleolus	Insert the needle perpendicularly for 0.3–0.5 *cun*
San Yin Jiao (SP 6)	On the tibial aspect of the leg, posterior to the medial border of the tibia and 3 *cun* superior to the prominence of the medical malleolus	Insert the needle perpendicularly for 1.0–1.5 *cun*
Shen Mai (BL 62)	On the lateral aspect of the foot, this acupoint is located directly inferior to the prominence of the lateral malleolus, in the depression between the inferior border of the lateral malleolus and the calcaneus	Insert the needle perpendicularly for 0.3–0.5 *cun*

**Figure 3 fig3:**
[figure not shown]
Acupuncture and sham acupuncture manipulation.

### Control group

Control acupoints will be used in this group, which are 1 cun laterally from the acupoints in the treatment group (shown in Figure 2), as we applied in previous research studies (12). Blunt needles with flat tips were selected for this study. After routine disinfection, acupuncture devices will be applied to each location. When the blunt needle tip penetrates the patch and touches the skin, the patient will experience a pricking sensation; however, no actual needle is inserted into the skin. With the patch, the needles are visually perceived as being inserted into the skin, mirroring the appearance of the treatment group. However, the acupuncturist will press the acupoints with a dry cotton ball to let the patient feel the ‘needles’ being withdrawn after treatment. Furthermore, the control group adheres to the same duration of needle retention, treatment time, and follow-up time as the treatment group.

Patients in both groups will receive sleep hygiene instructions, including recommendations to avoid consuming coffee, tea, or alcohol, maintain a regular sleep habit, create a quiet sleep environment, and promote a positive mood. If they experience severe discomfort caused by insomnia for two or more consecutive days, they are allowed to take hypnotic medications under the doctor’s guidance. However, the name of the medication, the doses, the date of administration, and the reactions to the medication will need to be recorded in detail on the case report form.

### fMRI examination

fMRI scans will be performed with an Ingenia 3.0 Tesla MRI scanner (Philips Medical Systems, Best, Netherlands) in the Department of Radiology at LongHua Hospital SHUTCM. During scanning, the participants are supine, with their heads immobilized and their ears plugged to minimize head movement and gradient noise interference. They will be instructed to wear black patches, close eyes, and remain still and awake throughout the process. Furthermore, the fMRI scans will be conducted by the same technician ([name]) using the same machine, and two qualified radiologists ([name] and [name]) will review the images for quality and procedure compliance after each scan, including the detection of any brain lesions or structural abnormalities. Both the technician and the radiologist have expertise in MRI imaging.

T1-weighted structural images are acquired with the following parameters: repetition time (TR) = 8.2 ms, echo time (TE) = 3.2 ms, slice thickness = 1.00 mm, slice number = 192, field of view (FOV) = 256 × 256 mm, flip angle = 8°, matrix size = 256 × 256 mm for standard space co-registration. Then the resting-state data are acquired as follows: repetition time (TR) = 2,000 ms, echo time (TE) = 30 ms, slice thickness = 3.5 mm, slice number = 33, field of view (FOV) = 224 × 224 mm, flip angle = 90°, and matrix size = 64 × 64 mm to obtain fMRI data. Scanning will be terminated if the participants feel any discomfort.

### Outcomes

The primary outcome measure is the treatment response rate, defined as the percentage of individuals whose total ISI score is decreased by ≥8 points from baseline at the end of treatment (week 4) (13).

ISI is a subjective and validated measure assessing various aspects of sleep, including sleep onset, maintenance, early awakening, dissatisfaction, interference with daytime functioning, life quality, and mental distress. The seven-item questionnaire uses a 0–4 scale, yielding a total score range of 0–28. Scores correspond to absence (0–7), mild (8–14), moderate (15–21), or severe (22–28) insomnia. The ISI is a concise, reliable tool commonly employed in general practice, sensitive to treatment response (14).

The secondary outcomes include the following eight items:

The change in ISI scores.The treatment remission rate: the percentage of people with ISI < 8.Actigraphy sleep assessment: It is a watch-shaped device to objectively record sleep patterns. It includes measurements of total sleep duration (TST), sleep–wake duration (WASO), and sleep efficiency (SE). Consequently, actigraphy serves as an effective tool for evaluating sleep quality in cancer patients (15).Generalized Anxiety Disorder Scale (GAD-7): It is a concise anxiety self-assessment instrument consisting of seven items scored on a 0–3 scale, yielding a total score range of 0–21. Scores of 5–9 indicate mild anxiety, 10–14 suggest moderate anxiety, and 15–21 represent severe anxiety (16).Patient Health Questionnaire-9 (PHQ-9): This nine-item validated depression self-assessment tool scored on a 0–3 scale, with a total score range of 0–27. Interpretation of scores categorizes depression as mild (5–9), moderate (10–14), severe (15–19), or very severe (20–27) (17).Quality of Life Core Scale (QLQ-C30): This 30-item questionnaire evaluates the QoL among cancer survivors. It comprises functional scales (physical, role, cognitive, emotional, and social functioning), a global QoL scale, symptom scales (fatigue, nausea and vomiting, and pain), and single items (appetite loss, diarrhea, dyspnea, constipation, insomnia, and financial impact) (18).The weekly usage of remedial drugs: The percentage of participants who used hypnotic medications.fMRI: The fMRI data will be pre-processed and analyzed using SPM8 software platform (SPM8, Wellcome Department of Imaging Neuroscience, London, United Kingdom) with MATLAB 2016b (MathWorks, Inc., Natick, MA, United States). Images will be pre-processed, including artifact correction (AFNI and RETRO-ICOR), head motion correction (FSL and MCFLIRT), and brain extraction (FSL and BET). Cortical surface reconstruction with boundary-based registration (FreeSurfer and bbregister) enhances structural–functional co-registration. After spatial smoothing and high-pass temporal filtering, various analytical methods (ALFF, ReHo, and seed-based FC) will assess neural response.

Outcomes will be measured during four different time points: week 0 (the baseline), week 1 (the intervention period), week 4 (the post-treatment period), and week 8 (the follow-up period). At week 0, ISI scores, actigraphy, GAD-7, PHQ-9, and QLQ-C30 will be collected. At week 4, the primary and all secondary outcomes will be tested. At week 1, actigraphy will be measured to observe the short-term effect of treatment. At week 8, the primary and a few secondary outcomes (i.e., the change of ISI scores, the treatment remission rate, and the weekly usage of remedial drugs) will be recorded. Additionally, at week 0 and week 4, neuroimaging data will be acquired to test the neural effects of the treatments for CRI patients, while the healthy subjects only need to be scanned once at week 0 (the baseline). Moreover, weekly usage of remedial drugs will be measured from week 1 to week 8.

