### Sample size calculation

Sample size calculation utilized the ‘Test For Two Proportions (Test Version)’ module of PASS software (version 15.0.5, NCSS, LLC) with a two-tailed α of 0.05, power of 80%, and a 1:1 ratio. Based on our preliminary pilot results, the treatment response rate at week 4 was 33.3% (5/15) in the treatment group and 6.7% (1/15) in the control group, with an effect size of 0.71. The sample size encompasses 32 participants allocated to each group. Assuming a 20% dropout rate, the required sample size is 40 participants per group, totaling 80 participants.

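### Entry at ISI 8 with response set at an 8-point fall makes some remissions count as primary failures, and no baseline-ISI adjustment is stated for the primary analysis

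*Protocol article*

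**What the plan says.** All references are to the protocol article.

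- **Criteria for inclusion:** the severity requirement is "Sleep severity index (ISI) score ≥ 8". No higher floor is set for the primary analysis.
- **Outcomes, primary:** response is the percentage of individuals "whose total ISI score is decreased by ≥8 points from baseline at the end of treatment (week 4"). This is an absolute fall, the same at every baseline.
- **Outcomes, scale:** the ISI is described as "yielding a total score range of 0–28", and "Scores correspond to absence (0–7), mild (8–14), moderate (15–21), or severe (22–28) insomnia".
- **Outcomes, secondary:** remission is "the percentage of people with ISI < 8". Change in ISI is a further secondary outcome.
- **Randomization, allocation concealment, and blinding:** random numbers from SAS and opaque envelopes are described. Stratification is not mentioned.
- **Statistical methods:** categorical variables get chi-square or Fisher's exact tests. Covariance analysis is planned for continuous data only.
- **Sample size calculation:** the test is planned "with a two-tailed α of 0.05, power of 80%, and a 1:1 ratio". From a pilot, "the treatment response rate at week 4 was 33.3% (5/15) in the treatment group" and 6.7% (1/15) in the control group. The result is 32 per group, or 40 after 20% dropout. The pilot's entry threshold and baseline ISI are not given.

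**The concern.** A fixed 8-point fall means different things at different baselines. At the entry floor it requires the complete disappearance of symptoms. At the top of the scale it can leave a patient with moderate insomnia. In the mild band the primary outcome can record loss of insomnia, by the article's own cut-off, as treatment failure.

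Two things are at stake. The first is interpretation: if the chance of response varies with baseline severity, the primary risk difference depends partly on the mix of severities recruited, and a reader cannot see this unless results are shown by severity. The second is precision of the comparison: with 40 per group, a chance imbalance in baseline ISI could shift the primary result, and the stated analysis of that binary outcome has no adjustment for it.

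**Working it through.** **1. The plan's own sample size.** Inputs: 5/15 and 1/15, two-sided α 0.05, power 80%.

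- Arcsine effect size: h = 2·asin√(5/15) − 2·asin√(1/15) = 0.709, matching the stated 0.71.
- n = 2(1.96 + 0.842)² / h² = 31.3, so 32 per group.
- Dropout: 32 / (1 − 0.20) = 40.

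The unpooled normal formula also gives 32 (31.4); the pooled formula would give 35. Exact power of the uncorrected chi-square test with 32 per group at these rates is 80.4%. The stated figures stand.

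**2. Definitions set side by side.** Let B be the baseline score and W the week-4 score. Response means W ≤ B − 8. Remission means W ≤ 7. Remission without response therefore means B − 7 ≤ W ≤ 7, which is possible only when B ≤ 14.

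| Baseline | Week-4 score needed to respond | Fall needed (8/B) | Remission but non-response |
|---|---|---|---|
| 8 | 0 | 100% | 1–7 |
| 9 | ≤ 1 | 89% | 2–7 |
| 10 | ≤ 2 | 80% | 3–7 |
| 11 | ≤ 3 | 73% | 4–7 |
| 12 | ≤ 4 | 67% | 5–7 |
| 13 | ≤ 5 | 62% | 6–7 |
| 14 | ≤ 6 | 57% | 7 |
| 15 | ≤ 7 | 53% | none |

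Of the 7 × 8 = 56 pairs of a mild baseline with a remission score, 7 + 6 + 5 + 4 + 3 + 2 + 1 = 28 are non-response. These are score pairs, not a proportion of patients. From baseline 16 upward the opposite can occur: 28 to 20 is a response, although 20 is in the moderate band.

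**3. Possible size, by simulation.** The documents give no baseline distribution, so all of the following is assumed: baseline mean 15, SD 4, restricted to 8–28; residual SD 4 at week 4; scores rounded and held within 0–28; improvement in each group set so that overall response is 33.3% and 6.7%. Two improvement models were compared.

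| | Proportional improvement | Same number of points for all |
|---|---|---|
| Share mild (8–14) | 43% | 43% |
| Acupuncture response, mild / moderate / severe | 22% / 40% / 61% | 33% / 33% / 33–34% |
| Sham response, across bands | 6–10% | 7% |
| Mild acupuncture patients in remission but non-responders | 28% | 29% |

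On these assumptions about 0.43 × 0.28 = 12% of the acupuncture group, or 0.12 × 40 ≈ 5 patients, would be in remission and counted as failures. With an assumed baseline mean from 13 to 17 (proportional model), the mild share runs from about 62% to 26%, and remission without response from about 33% to 24% of mild acupuncture patients.

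**The case against.** Response and remission are separate endpoints, and nothing obliges one to imply the other. Losing some information is a known price of a dichotomised outcome. The 8-point criterion carries a citation, and benefit in mild patients is still recorded through remission and change in ISI. Entry also requires a DSM-IV diagnosis lasting at least a month, so few patients near ISI 8 may enrol. The article is condensed, so silence on stratification does not prove there is none, and chance imbalance does not bias a randomised test. All of this stands. It limits the point to a mismatch of unknown size, but it does not remove the mismatch or supply a baseline adjustment for the primary outcome.

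A reader might go further in three ways that the documents do not support.

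- **That the trial is underpowered because of mild patients.** This requires the pilot rates to apply only to patients at ISI 15 or above. The article does not say so. If the pilot used the same entry rule, its rates already include the effect and power is about 80%.
- **That mild patients have almost no chance of responding.** Response is hardest at baselines 8–10, but the proportional model still gives 22% across the mild band on acupuncture, and the equal-points model gives the same 33% as elsewhere. Whether the risk difference varies with severity at all depends on a model the documents do not settle.
- **That entry should be raised to ISI 15.** That changes the population under study, would exclude about 43% of patients on the assumption above, and would leave it unclear whether the pilot rates still apply.

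**Conclusion.** The definitional mismatch is certain. Entrants at ISI 8–14 must reach 0–6 to respond, and at each of those baselines there are week-4 scores that meet the remission definition but fail the primary outcome. Its extent cannot be computed from the documents. The figures of about 43% mild, and about 28–29% of mild acupuncture patients in remission but non-responders, rest on an assumed mean of 15 and SD of 4. The second figure is nearly the same under both improvement models; the gradient of response across severity bands is not. The sample size is not in error. What merits a change is that the stated primary analysis makes no allowance for a baseline score that the trial already collects, and that the planned reporting would not show remissions counted as failures.

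**What to change.** Keep the entry criterion and the primary endpoint, and make three changes.

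1. If the randomisation list can still be changed, stratify it by baseline ISI, 8–14 versus 15 or more. If stratification is already in the full protocol, state it.
2. Replace the unadjusted chi-square or Fisher test for the primary outcome with a baseline-adjusted analysis: a Mantel-Haenszel risk difference over these two strata, or a model that includes baseline ISI. The adjustment can be made even if the list cannot be changed.
3. Report response and remission cross-classified by group within each stratum, so that remission counted as non-response is visible.

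The cost is a new randomisation list (for the first change only), revised analysis wording and one more table. The gain is protection against chance imbalance and a visible dependence on case mix. It should not be presented as a gain in power: simulated power is about 80% with or without it. The changes do not alter the endpoint, so a patient going from 14 to 7 remains a non-responder; the table makes that explicit.

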### Statistical methods

Statistical analysis will employ SAS software for the full analysis set, per-protocol set, and safety set. Missing values will be handled using the last observation carryover method. Continuous variables will be presented as mean ± SD (normal distribution) or median (range) (non-normal distribution) and assessed with the t-test or Mann–Whitney U test. Categorical variables will be presented as frequencies or percentages and analyzed using chi-square or Fisher’s exact tests. CIs will be set at 95% with a significance level of 5% (*p* < 0.05). To avoid multiplicity, we will use a Bonferroni adjustment for multiple comparisons of fMRI among the treatment group, control group, and healthy subjects. With three groups (k = 3), the adjusted test level (α’) was set at 0.0167 (α/3 = 0.05/3). Pearson’s correlation will examine the association between changes in brain activity and clinical outcome improvement within each group. The success of blinding will be assessed using the Bang’s Index. In addition, to mitigate the influence of age and other confounding factors, we will employ covariance analysis on the continuous data.

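### The stated imaging order smooths the data before ReHo, which raises ReHo mechanically and, depending on a kernel that is not given, lowers its sensitivity to group differences

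*Protocol article*

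**What the plan says.** The last secondary outcome in the Outcomes section is fMRI. After listing the correction and registration steps, it says: "After spatial smoothing and high-pass temporal filtering, various analytical methods (ALFF, ReHo, and seed-based FC) will assess neural response". ReHo is named alongside the other two measures and is not exempted. Nothing says that ReHo maps are smoothed after they are computed. No kernel width or ReHo neighbourhood is given.

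The fMRI examination section gives the resting-state geometry: "field of view (FOV) = 224 × 224 mm", "matrix size = 64 × 64 mm to obtain fMRI data" and "slice thickness = 3.5 mm".

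Statistical methods uses the imaging measures twice. One use is a group comparison with a "Bonferroni adjustment for multiple comparisons of fMRI among the treatment group, control group, and healthy subjects", tested at 0.0167. The other is a correlation analysis: "Pearson’s correlation will examine the association between changes in brain activity and clinical outcome improvement within each group".

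**The concern.** ReHo is an index of local agreement: the concordance of a voxel's time series with those of the voxels around it. Spatial smoothing replaces each voxel by a weighted average of the same neighbours. If smoothing comes first, part of the agreement that ReHo reports has been put there by the filter, even where the brain signal has none. This follows from the definition of the measure. ALFF is computed voxel by voxel and seed-based FC relates a voxel to a seed, so neither has this particular problem.

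At stake is the usefulness of one of the three named imaging measures. Neural mechanism is a stated aim of the trial, and the comparisons are already small, with 40 patients planned per arm and 10 healthy subjects. If the scale is pushed upwards and differences are squeezed, a null ReHo result could reflect the processing order rather than the absence of an effect.

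**Working it through.** **Plan figure.** The protocol gives no figure for ReHo. Its sample size concerns the ISI response rate only. It can be reproduced (arcsine effect size 0.709; 2 × ((1.960 + 0.842)/h)² ≈ 31.3, so 32; 32/0.8 = 40) and plays no part below.

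**Inputs from the protocol.** In-plane voxel 224/64 = 3.5 mm, reading the matrix as 64 × 64 voxels. Slice thickness is 3.5 mm, so voxels are isotropic if there is no slice gap (assumption).

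**Assumptions, none stated in the protocol.** Kernel FWHM of 4, 6 or 8 mm; 27-voxel neighbourhood; spatially white noise; a shared-signal fraction rho that is higher in one group.

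**Step 1: pure noise.** For Gaussian series with correlation r, the expected rank correlation is (6/π) arcsin(r/2). With mean rank correlation m over all pairs of the 27 voxels, W = (1 + 26m)/27. The kernel SD in voxels is FWHM/2.355/3.5.

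| Kernel | m | W |
|---|---|---|
| none | 0 | 1/27 = 0.037 |
| 4 mm | 0.0478 | (1 + 1.243)/27 = 0.083 |
| 6 mm | 0.2233 | (1 + 5.806)/27 = 0.252 |
| 8 mm | 0.3886 | (1 + 10.104)/27 = 0.411 |

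The kernel alone multiplies W by about 2, 7 and 11.

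**Step 2: with real local signal.** For a signal with 8 mm spatial extent and rho = 0.4, W is 0.185 unsmoothed and 0.319, 0.495 and 0.588 after 4, 6 and 8 mm. The rise is (0.319 − 0.185)/0.319 = 42% of the smoothed value at 4 mm, and likewise 63% and 69% at 6 and 8 mm.

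**Step 3: contrast between groups on the W scale.** Seven rho contrasts were crossed with three signal types (fully shared, 8 mm, 12 mm), giving 21 scenarios. The ratio of W between groups moved towards 1 in all of them at every kernel. The absolute difference behaved less uniformly. For rho 0.4 vs 0.5 with an 8 mm signal it went from 0.037 to 0.034, 0.013 and 0.006. For rho 0.05 vs 0.15 with the same signal it grew from 0.037 to 0.083 at 6 mm.

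**Step 4: standardised difference.** Smoothing also shrinks the spread between subjects, so power has to be judged on d, the difference divided by the SD. Two sets of simulations assumed a between-subject SD of rho of 0.1.

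| Signal, rho | none | 4 mm | 6 mm | 8 mm |
|---|---|---|---|---|
| 8 mm, 0.3 vs 0.4 (set A) | 0.94 | 0.92 | 0.72 | 0.47 |
| 8 mm, 0.4 vs 0.5 (A) | 0.87 | 0.70 | 0.22 | 0.05 |
| 12 mm, 0.3 vs 0.4 (A) | 0.89 | 0.88 | 0.75 | 0.56 |
| 12 mm, 0.4 vs 0.5 (A) | 0.97 | 0.91 | 0.67 | 0.43 |
| shared cluster, 0.3 vs 0.4 (set B) | 0.92 | 0.90 | 0.81 | 0.76 |
| 8 mm signal (B) | 0.94 | 0.84 | 0.49 | 0.26 |

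Set A used 60 subjects per group and one seed, so a single d near 0.9 has a standard error of about √(120/3600 + 0.81/240) = 0.19. Columns within a row share the same data, so differences along a row are steadier than that. A further repeat found losses of about 3–16% at 4 mm, roughly 20–30% in the cluster model, and up to about 90% at 8 mm with a spatially smooth signal.

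**Step 5: the alternative order.** In set A, computing W first and then averaging the map over 27 voxels, a stand-in for smoothing afterwards, kept d at 0.91–0.96 in all four cases.

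**The case against.** The best defence is that this is a journal article summarising an imaging plan in a few lines. It names several software packages and omits kernel, filter cut-off, seeds and neighbourhood. One introductory clause covering three measures may be condensation rather than a decision to smooth before ReHo. That is possible, and it makes the remedy lighter. It does not remove the point: the sentence is not silent on order but states one, and an analyst following it would smooth first.

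The second defence is that every scan is processed alike, so the spread shrinks with the difference and power need not suffer. This stands in part. In the shared-cluster case the raw gap for rho 0.3 vs 0.4 fell from 0.086 to 0.017 at 8 mm, while d fell only from 0.92 to 0.76, about 17%. With spatially smooth signals, however, d itself fell substantially at 6–8 mm.

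A reader might infer more: that ReHo would mostly measure the filter, or that the collapse of a raw gap shows the loss of power. The documents do not support either as a general statement. The kernel is not given; at 4 mm the inflation is under half of the smoothed value in the worked case and the loss of d is mostly small. Absolute differences can even grow where concordance is very low, and raw gaps overstate the loss of power.

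**Conclusion.** The point holds in limited form. As written, the plan computes ReHo on smoothed data. That raises it mechanically, from 0.04 to about 0.08, 0.25 or 0.41 in pure noise for 4, 6 or 8 mm kernels, and tends to lower its sensitivity to group differences. The loss is small at 4 mm and moderate to large at 6–8 mm: a standardised difference of about 0.9 typically becomes 0.5–0.8 and 0.3–0.7 respectively. The simulated extremes at 8 mm run from 0.76 to 0.05. These sizes rest on the assumed kernels, 27-voxel neighbourhood, white noise, signal extent and between-subject SD; the direction of the inflation does not.

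The consequence is confined to one of three measures within one of eight secondary outcomes. The ISI response rate and the other clinical outcomes are untouched. A reader might also suspect bias between acupuncture and sham or an excess of false positives; the same smoothing applies to all groups and neither is shown.

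**What to change.** State in the fMRI item that ReHo is computed on the unsmoothed, temporally filtered data and that the resulting ReHo maps are smoothed afterwards. Keep the present order for ALFF and seed-based FC. If separate pipelines were always intended, one clause exempting ReHo from prior smoothing settles it. Giving the kernel width and ReHo neighbourhood in the same sentence would let a reader judge any remaining effect.

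The cost is one clause of text and a small change to the processing script. No new scans or participants are needed, and no other outcome changes. The protocol's Study design section commits to reporting modifications to the registry and the ethics committee, so the change should be notified there, preferably before any group maps are examined.
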